## Abstract

**Background:**

Juvenile justice (JJ) youth are at high risk of opioid and other substance use (SU), dysfunctional family/social relationships, and complex trauma. The purpose of the Leveraging Safe Adults (LeSA) Project is to examine the effectiveness of Trust-Based Relational Intervention® (TBRI®; leveraging family systems by providing emotional and instrumental guidance, support, and role modeling) in preventing opioid and other SU among youth after release from secure residential facilities.

**Methods:**

An effectiveness-implementation Hybrid Type 1 design is used to test the effectiveness of TBRI for preventing non-medical use of opioids among JJ-youth (delayed-start at the site level; a randomized controlled trial at participant level) and to gain insight into facility-level barriers to TBRI implementation as part of JJ re-entry protocols. Recruitment includes two samples (effectiveness: 360 youth/caregiver dyads; implementation: 203 JJ staff) from nine sites in two states over 3 years. Participant eligibility includes 15 to 18-year-olds disposed to community supervision and receiving care in a secure JJ facility, without active suicide risk, and with one caregiver willing to participate. Effectiveness data come from (1) youth and caregiver self-report on background, SU, psychosocial functioning, and youth-caregiver relationships (Months 0, 3, 6, 12, and 18), youth monthly post-release check-ins, and caregiver report on youth psychological/behavioral symptoms, and (2) JJ facility records (e.g., recidivism, treatment utilization). Fidelity assessment includes post-session checklists and measures of TBRI strategy use. Collected four times over four years, implementation data include (1) JJ staff self-report on facility and staff characteristics, use of trauma-informed care and TBRI strategies, and (2) focus groups (line staff, leadership separately) on use of trauma-informed strategies, uptake of new interventions, and penetration, sustainment, and expansion of TBRI practices.

**Discussion:**

The LeSA study is testing TBRI as a means to empower caregivers to help prevent opioid use and other SU among JJ-youth. TBRI’s multiple components offer an opportunity for caregivers to supplement and extend gains during residential care. If effective and implemented successfully, the LeSA protocol will help expand the application of TBRI with a wider audience and provide guidance for implementing multi-component interventions in complex systems spanning multiple contexts.

**Trial registration:**

ClinicalTrials.govNCT04678960; registered November 11, 2020; https://clinicaltrials.gov/ct2/show/NCT04678960.

## Background

Across the US, an estimated 10.8 million people misuse prescription opioid analgesics (including prescription opioids and illicit opioids, such as heroin and illicitly made fentanyl and related analogs) [1]. Sixty percent of overdoses are attributed to opioids [2, 3], which are now the 5th leading cause of accidental death [4]. Experimentation and regular use of opioids escalate in the late teens and early 20s [5–8]. Nationally, 16.6 million youth aged 14–17 are involved in the US juvenile justice (JJ) system [9], making it a critically important intervention opportunity [10]. Substance use (SU) among JJ youth is associated with deviant behavior and recidivism [11, 12], physical and mental health (MH) problems [13–16], and places youth at higher risk for non-medical use of opioids [17].

SU risk is heightened among youth who are transitioning back into their communities after a period of residential detainment or treatment and especially among those who have a history of adverse childhood experiences (ACEs) leading up to JJ involvement [18]. Living arrangements can be tentative, family support for rehabilitation unstable, the means to pursue vocational and/or educational goals may be sparse, and families may have limited access to (or knowledge of) available supports. Many youth return to behaviors, thinking patterns, and social groups that are familiar and negative [19]. It is therefore imperative that opioid prevention interventions assist youth (particularly those with childhood trauma) in developing relationships with adults who serve as positive guides and mentors through their transition into young adulthood.

Trauma is particularly problematic among JJ youth [20]. Adverse childhood experiences underlying trauma are risk factors to MH disorders [21, 22]; earlier onset of opioid and other SU, drug overdose [23]; and use in young adulthood [24, 25]. Furthermore, complex trauma (i.e., chronic and repeated exposure) is associated with offending and recidivism [26] [27]. Because protective relationships with adults can moderate the relationship between ACEs and SU [20] [28], addressing trauma as part of interventions to prevent opioid initiation is critically important [21].

Strong family relationships [29], healthy attachment bonds [30], and support systems that foster positive coping and emotional autonomy [31] are robust protective factors against SU. However, many families are ill-equipped to provide effective guidance and support, lacking knowledge and experience in how to interact in supportive and nurturing ways, and effectively direct youth toward healthy independence and autonomy [32]. Interventions are needed that systemically address risk factors for opioid/SU with complementary cognitive-behavioral (change thoughts, beliefs, and behaviors) and relational approaches (improve trust, emotional regulation, appropriate parental response) [33–35]. Given that youth discharged from secure residential facilities often return to existing family/living environments, empowering the adults who are responsible for their care with effective tools and support is necessary and represents an urgent and potentially transformative prevention/intervention opportunity.

The purpose of the Leveraging Safe Adults (LeSA) Project is to examine the effectiveness of Trust-based Relational Intervention® (T﻿BRI) [36, 37] in preventing opioid and other SU among youth after release from secure residential facilities. The primary aim is to leverage existing relationships to more effectively support youth after returning home. Caregivers are trained to be “safe adults” for their youth, by building trust, practicing authentic communication, developing boundaries, and setting realistic expectations in order to proactively and effectively identify and address their youth’s needs. Through their relationships with safe adults, youth learn and practice self-regulation, enabling them to more effectively refrain from opioid use, other SU, and other risky activities.

As depicted in Fig. 1, youth enter the JJ system (and subsequent secure residential settings) with significant risk for SU. TBRI is designed to strengthen relationships by improving the connection between youth and caregiver, empowering caregivers to identify and address youths’ physiological and emotional needs, and equipping caregivers with effective tools for correcting inappropriate behavior while maintaining healthy connection [36, 38]. By simultaneously addressing the underlying pillars of trauma-informed care (e.g., connection, self-regulation) [39, 40], caregivers learn effective support and response strategies, and youth learn to develop healthy relationships and practice self-regulation in an emotionally safe environment. This in turn strengthens trust and feelings of emotional safety, which promotes better decision-making and healthy lifestyle choices (including lower SU).

**Fig. 1 Fig1:**
[figure not shown]
LeSA Project Conceptual Framework. *Note*. TBRI® = Trust-based Relational Intervention®

Because a high proportion of JJ youth has complicated living situations (e.g., child welfare involvement after allegations of abuse or neglect) [41], the term “safe adult” includes guardians (e.g., grandparent, aunt/uncle) as well as biological, adoptive, and foster parents. Safe adults (to whom youth will likely be released, determined by the presiding Judge and/or court system) agree to support the youth’s transition back to the community by providing housing and carrying out post-release plans (e.g., encouraging engagement in school and/or employment; helping navigate social and emotional challenges; transporting them to appointments). If successful, this project will provide a family-centered intervention for adolescents that can be implemented by JJ agencies and/or other social service agencies that intersect with JJ as part of re-entry services.

## Methods/design

### Research aims

The specific aims of the LeSA Project are to: (1) test the effectiveness of the TBRI intervention and its different support formats – no in-home TBRI support, Structured Coaching, Responsive Coaching – on (a) preventing initiation and/or escalation of opioid use, (b) public health and public safety outcomes, (c) putative change mechanisms, including self-regulation, psychosocial functioning, and relationship with a safe adult; (2) document factors related to TBRI implementation and sustainment; and (3) estimate the start-up and implementation costs and cost-effectiveness of TBRI support options relative to standard re-entry practices in achieving lower rates of opioid initiation and reductions in healthcare and JJ system costs.

Primary hypotheses are as follows:
H1: Compared to youth receiving Standard Re-entry Practices (SRP) only, youth receiving TBRI in addition to SRP are less likely to initiate opioid use following discharge.H2: Compared to no in-home TBRI support, youth receiving Structured or Responsive Coaching are less likely to initiate opioid use following discharge, with the longest time to initiation occurring among youth receiving Responsive Coaching.H3: TBRI is most effective for preventing opioid initiation when facilities routinely use TBRI strategies within their residential settings, given increases in continuity as the youth transitions home from residential care.H4: The cost of implementing TBRI + SRP is higher than SRP alone, with higher cost-effectiveness when TBRI is added.

### Trust-based Relational Intervention®﻿

TBRI ﻿is a whole-child, attachment-based, trauma-informed intervention that promotes emotional regulation through interaction with responsive adults. The model is grounded in attachment theory and research [42, 43], emphasizing mindful awareness and engagement between adults and children as a means of building trust and resilience [37]. TBRI is also designed to address relational trauma, for instance, in the three pillars of trauma-wise care: felt-safety, connection, and self-regulation [39, 40]. The three evidence-based principles of TBRI include connection, empowerment, and correction [37]. Each principle includes a set of specific strategies that address social, behavioral, emotional, physiological, cognitive, and ecological aspects of children’s development and well-being (see Table 1).

**Table 1 Tab1:** TBRI Principles and Strategies

TBRI Principle	TBRI Strategies	Examples
Connection (relationships and attachment needs)	Engagement	Appropriate touch, eye contact, playful interaction, behavior matching or mirroring
	Mindfulness	Empathy, receptive communication, physical presence, removing fears, felt safety, awareness
Empowerment (physical needs)	Physiological	Nutrition, hydration, sensory needs or factors, snacks, sleep and rest, physical activity
	Ecological	Rituals, schedules, transitions (e.g., creating transitional plan for youth re-entry), artifacts (e.g., “brain” hats, coloring workbooks)
Correction (behavioral needs; disarm fear-based behaviors and teach appropriate social skills)	Proactive	Life Value Terms (with respect, using words, gentle and kind), behavioral scripts, choices, compromises, “redos”
	Responsive	IDEAL Response (i.e., correction needs to be immediate, direct, efficient, action-based, leveled at behavior), Levels of Response (i.e., redirect using the least corrective effort, from playful, structured, calming, to protective engagement; “keep it low”)

*Note*. Please see Purvis (Purvis et al., 2013) for a detailed description of these TBRI strategies

The *primary TBRI intervention* is delivered while youth are in secure residential settings, within 3 months prior to discharge. Principles and strategies are learned and practiced in separate caregiver and youth group sessions, then strengthened in joint youth-caregiver sessions. The focus of caregiver sessions is on identifying and meeting youth needs, supporting appropriate self-expression, improving self-regulation, and developing healthier relationships. Youth are also trained in complementary sessions to develop skills and a deeper understanding of felt safety and trust. Key constructs are taught through playful engagement and role play for youth and caregivers to actively connect with one another while developing new skills.

The *primary TBRI intervention* is an adapted version of the TBRI Caregiver Curriculum [33, 37] and includes several components (see Tables 2-3): (1) Youth Trainings: 9, 45-min youth-only modules; (2) Caregiver Trainings: a 1-h individual introductory module and 9, 90-min caregiver-only modules; and (3) Nurture Groups: Youth and caregivers participate together in 4, 1-h joint-roleplay sessions. Both Youth and Caregiver Trainings are designed to be delivered in a group setting with three to five in each group; however, missed sessions can be delivered as individual sessions. Additional monthly “booster” nurture group sessions are delivered in instances where the youth’s discharge is extended beyond the original expected date.

**Table 2 Tab2:** A Brief Overview of TBRI Curriculum (Caregiver Trainings, Youth Trainings, Nurture Groups)

Primary TBRI Intervention			
**Module**	**Youth and Young Adult Curriculum **	**Caregiver Curriculum**	**Nurture Group Activity (joint roleplay by youth/caregivers)**
0	• Introductions and Expectations • Familiarization with the Virtual Platform • Overview of the Tools for Learning and the Youth Workbook • Group rules: Designed for Felt Safety among all Participants	• Introductions and Expectations • Familiarization with the Virtual Platform •Overview of the Tools for Learning and the Caregiver workbook • Group rules: Designed for Felt Safety among all Participants	• N/A
*Session 1: TBRI: Introduction and Overview*			
1	• Explanation of a whole-person approach • Building relationships grounded in connection. • Overview of TBRI Principles	• Understanding TBRI, Risk Factors and Brain Growth • Overview of TBRI Principles	• Divided Line Drawing: Current versus future family • Begin communicating/ negotiating changes needed
2	• Balancing Structure and Nurture • Caregiving Styles • Preparation for TBRI Nurture Groups	• Balancing Structure and Nurture • Caregiving Styles • Preparation for TBRI Nurture Groups	
*Session 2: Connecting Principles*			
3	• Attachment • Four Hallmarks of a Secure Adult • Rupture and Repair • The Importance of an Apology	• TBRI Connecting Principles • Attachment	• Role Play: Apologizing • Modeling connecting after a rupture in the relationship
4	• Connecting • Mindfulness • Emotional Safety	• Mindfulness • Adult Attachment • TBRI Engagement Strategies	
*Session 3: Empowering Principles and Correcting Principles: Proactive Strategies*			
5	• Understanding the components of a Nurture Group	• TBRI Empowering Principles • Physiological Strategies • Sensory input and needs • Ecological Strategies	• Creating a Family Life Value Terms List • Communicating about strategies family will use upon the youth’s transition home
6	• Balancing Structure and Nurture • Practicing supportive communication	• TBRI Correcting Principles: Proactive Strategies • Choices, Compromises, Sharing Power • Life Value Terms	
*Session 4: Correcting Principles: Responsive Strategies*			
7	• Ecological Strategies • Three goals of correction: connection, contentedness, and changed behaviors	• Review of Correcting Principles: Proactive Strategies • The IDEAL© Response	• Role Play: Supportive vs. aggressive communication style • Engage in conversation about changes in family dynamics
8	• Power Struggles and Sharing Power • Life Value Terms • Role Play-IDEAL© Response • Graduation	• Levels of Response© • Applications using case studies • Graduation	

*Note*. The overall goals of this program include developing a spoken TBRI language and understanding for the youth to relate to their caregiver. They will be given voice, gain an understanding of self-awareness, develop autonomy, and most importantly, felt safety. This program is deeply rooted in connection, mindfulness, and trust

**Table 3 Tab3:** A Brief Overview of TBRI In-Home Training Curriculum

Secondary TBRI Intervention		
**Module**	**In-Home Coaching Curriculum**	**Support Formats**
*Goals: (1) Creating an environment of felt-safety between coach and family and encourage felt-safety between family members (2); Facilitating a discussion about healthy relationships that meet the needs of all family members; and (3) Practicing strategies for engagement and mindful awareness.*		
1	• Felt Safety • Felt-safety in relationships • Strategies for building felt-safety	• *Structured Coaching: Required* • *Responsive Coaching: Required*
2	• Building Healthy Relationships • 4 Skills of Healthy Relationships • TBRI Connecting Strategies	
*Goals: (1) Creating space for an ongoing dialog about balancing structure and nurture in the caregiver-youth relationship (2); Practicing looking for the need behind the behavior (3); Engaging caregivers and youth in considering what shared power looks like in their family; and (4) Practicing setting the bar for growth and success.*		
3	• Balancing Structure and Nurture • Rethinking discipline • The meaning behind the behavior • Negotiating needs	• *Structured Coaching: Required* • *Responsive Coaching: Optional*
4	• Sharing Power • Obstacles to sharing power • Self-worth & autonomy • Appropriate expectations	
*Goals: (1) Discussing how stress changes our brain, and (2) Discussing using brain development as a lens to view adolescence.*		
5	• Toxic Stress and the Brain • The teen brain • Adverse Childhood Experiences	• *Structured Coaching: N/A* • *Responsive Coaching: Optional*
*Goals: (1) Returning to the topic of healthy relationships, and (2) Engaging the family in a deeper dive of how relationships shape lives.*		
6	• Adult Attachment • Experiences in close relationships • Earned security	• *Structured Coaching: N/A* • *Responsive Coaching: Optional*
*Goal: Building mindfulness practices to increase awareness of self, others, and situation*		
7	• Mindfulness • Grounding/breathing techniques • Self-care	• *Structured Coaching: N/A* • *Responsive Coaching: Optional*
*Goal: Discussing sensory processing with a focus on identifying and meeting specific sensory needs*		
8	• Sensory Experiences • Sensory profile self-assessment • Sensory resources	• *Structured Coaching: N/A* • *Responsive Coaching: Optional*
*Goals: (1) Creating space for discussing challenges around the family’s current transitions, and (2) Anticipating future transitions*		
9	• Life Transitions • Predictability and uncertainty • Detective diaries	• *Structured Coaching: N/A* • *Responsive Coaching: Optional*

*Note*. Sessions can be repeated with families who choose to continue coaching over a longer period of time (responsive coaching condition only)

The *secondary TBRI intervention* is provided after completion of the primary intervention and includes in-home support following discharge. Youth and caregivers randomly assigned to Coaching receive either Structured (4 TBRI In-Home Trainings) or Responsive Coaching (2+ TBRI In-Home Trainings with additional trainings as requested by the family or triggered by SU or risk factors observed/identified by research staff).

For the purpose of this project, TBRI intervention components are delivered by 1–2 Research Assistants (RAs) who are also trained as TBRI Practitioners. All TBRI Practitioners have a minimum Bachelor’s Degree in human services areas, more than 2 years of clinical experience and fieldwork in high-risk juvenile and adult populations, receive a minimum of 20-h onboard training and skills development as well as ongoing training/supervision. All caregiver sessions are delivered virtually to enable caregivers who do not live close to the site where their youth resides. Sessions are synchronous, and participants are provided an “orientation” to the online platform prior to the first session. Youth sessions are delivered in person at the facility by RAs, with support from non-correctional staff (e.g., clinical staff). Nurture groups are delivered in a group format with youth joining virtually as a group from the facility and caregivers joining individually from their homes. Sites determine when and where youth sessions will be delivered, including which staff to involve (i.e., therapeutic staff who could participate in intervention activities. Staff are provided training on logistics and strategies to address potential behavioral issues and support a youth in need.

In addition to the features described above, TBRI also serves as a multi-systemic caregiving model that has been successfully implemented in a wide variety of professional contexts [44] [45] [46] [47]. TBRI can be implemented by anyone trained in the tools and strategies, and therefore provides a framework and impetus for empowering all adults, regardless of status or education, to be catalysts of change for youth. Therefore, TBRI can be implemented across an entire JJ system to facilitate the use of trauma-informed approaches in all interactions. For the purpose of this project, the implementation of TBRI principles and strategies within the broader residential context is referred to as the *organizational TBRI intervention*.

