### Hybrid design: effectiveness trial

The effectiveness trial includes a comparison of youth enrolled in SRP to youth enrolled in SRP plus TBRI, whereby each facility serves as its own control. Because caregivers may need support after their youths’ release, three versions of TBRI are compared, with youth in the SRP + TBRI cohort being randomly assigned to one of three support formats: (1) TBRI Training only (no in-home TBRI support), (2) TBRI Training + Structured Coaching (4 sessions), and (3) TBRI Training + Responsive Coaching (2+ sessions, triggered by youth need/risk).

The effectiveness trial proceeds in 3 stages: Standard Reentry Practice (SRP) only (baseline control), SRP + TBRI, and Facility Sustainment (see Fig. 2). **Stage 1 - SRP**: sites engage in standard practice; study activities include youth and caregiver assessments over 18 months. Each site serves as its own control. A total of 120 youth/adult dyads are recruited across the nine sites. The length of SRP varies between 8 months (Wave 1) and 12 months (Wave 3). **Stage 2 - SRP + TBRI Intervention:** sites continue to engage in standard practice; TBRI intervention is delivered to youth and caregivers enrolled in the study; youth and caregiver assessments are conducted over an 18-month period. A total of 240 youth/adult dyads are recruited across the nine sites. **Stage 3 - Facility Sustainment**: youth/caregiver recruitment, baseline assessment, and interventions cease; youth and caregiver follow-up interviews continue; responsibility for implementing primary and secondary TBRI intervention components is transferred to the JJ facility.

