#### Power

For H1 examining the effectiveness of SRP + TBRI compared to SRP alone, the proposed Intent to Treat (ITT) sample will include 360 youth/safe adult dyads (120 SRP, 240 TBRI), with 80 randomized to each TBRI condition. SAS PROC POWER for rank tests comparing 2 survival curves found that, if overall opioid initiation rates are 35% (SRP) vs. 25% (all TBRI groups) at any assessed time point, power is estimated to be at 93% (*α* = .05). For H2 comparing the 3 TBRI conditions, SAS PROC POWER for rank tests comparing 2 survival curves found that for sample sizes of 80 in each group, power = .80 when the hazard ratio = 1.57. When the combined TBRI groups are tested against SRP, power = .80 when the hazard ratio = 1.37.

For H3 and H4 pertinent to the organizational TBRI intervention, the expected sample (nine sites, up to 90 staff participants per site) and the response rate of 25% gives an expected sample of 203 participants. A small effect size (0.20), a power of 0.80, significance level of 0.05, and an intraclass correlation of 0.10 are used to calculate the minimum required sample size. Repeated measures design comparing staff participants over time results in a minimum sample size of 43 participants. To be more conservative, the same parameters are used for a mixed-effect design (four repeated measures by nine sites), yielding a minimum sample size of 189 participants.

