### Data analysis plan

For all analyses, an ITT approach is used, where all study participants are included in analyses. For H1 and H2, comparisons of survival curves for each group are performed using SAS PROC PHREG and PROC GLIMMIX using the log rank test with the Sidak multiple-comparison adjustment, with the primary outcome as the dependent variable. Differences between groups on secondary outcomes and change over time in implementation measures (e.g., TBRI use) are examined using repeated measures ANOVAs (SAS 9.4, PROC MIXED), with study site as random effects and condition, time, and interactions as fixed factors. Because SU rates are generally lower among JJ females, sex as a biological variable is examined as a moderator of differences in outcomes using univariate analyses (e.g., chi square, t-tests, ANOVA); when significant, tests of moderation are undertaken as part of all analyses. Putative change mechanisms are investigated as mediators of the Group – Primary Outcome relationship and structural equation modeling (SEM; using Mplus) is used to examine sex differences in mediation. For H3, changes in the outcomes over time are examined using repeated measures ANOVAs (SAS 9.4, PROC MIXED), with study site as random effects and time and time × site interactions as fixed factors. For H1–3, a log rank test is used to assess study dropout; stochastic multiple-imputation provides maximum likelihood estimates, accounts for uncertainty in missing values, and provides unbiased estimates of the treatment effect if data are missing at random.

Qualitative data from focus groups are transcribed and qualitatively coded (in Atlas.ti) by at least 2 research staff. An iterative process of coding and thematic analysis [84] are used to understand routine practices employed, nuances in the use of trauma-informed and child-centered strategies, facility facilitators/barriers to uptake of new interventions, general penetration of TBRI within the facility, and facility interest in sustaining and/or expanding TBRI practices.

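### TBRI is taught in groups of three to five, but the H1 and secondary analyses name no training-group term, so SRP-versus-TBRI standard errors may be understated

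*Protocol article*

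**What the plan says.** On delivery, the section on the Trust-based Relational Intervention says: "Both Youth and Caregiver Trainings are designed to be delivered in a group setting with three to five in each group". It allows an exception: "however, missed sessions can be delivered as individual sessions". The four joint sessions are grouped as well: "Nurture groups are delivered in a group format with youth joining virtually as a group from the facility". One or two research assistants deliver the components.

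For the control stage, the section Hybrid design: effectiveness trial says only that "sites engage in standard practice; study activities include youth and caregiver assessments over 18 months". It describes no study-run groups.

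The Power section plans "360 youth/safe adult dyads (120 SRP, 240 TBRI), with 80 randomized to each TBRI condition". Its H1 calculation is a rank test of two survival curves with no design effect. The only intraclass correlation in the article, 0.10, belongs to the staff sample.

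The Data analysis plan gives the secondary-outcome model as repeated measures ANOVA in PROC MIXED, "with study site as random effects and condition, time, and interactions as fixed factors". For H1 and H2 it names PROC PHREG, PROC GLIMMIX and a log-rank test with a Sidak adjustment, and no cluster term. The H4 cost models are described separately, with clustering at facility or provider level and bootstrapped intervals.

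**The concern.** Dyads in the TBRI cohort go through nine youth modules, nine caregiver modules plus an introductory one, and four joint sessions, mostly in small groups. The curriculum works through role play and interaction, so group-mates may come to resemble one another in outcome. Nothing comparable is described for SRP. Clusters that arise from treatment in one arm only make a partially nested design.

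A random site effect takes up the correlation shared by everyone at a facility. It does not take up extra correlation among the three to five dyads taught together within that facility. For H1 no cluster term is named at all, not even site. If the extra correlation is positive, the information in the TBRI arm is overstated. H1 and the secondary SRP-versus-TBRI contrasts would then have intervals that are too narrow and an error rate above nominal.

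H2 is barely affected. Dyads are randomised individually to the three support formats at discharge, after the group phase, so the formats cut across training groups.

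**Working it through.** **The plan's own figure.** The H1 power statement assumes: "if overall opioid initiation rates are 35% (SRP) vs. 25% (all TBRI groups) at any assessed time point". It reports 93% power at α = .05.

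- Expected events: 120 × 0.35 + 240 × 0.25 = 42 + 60 = 102.
- Hazard ratio implied by the rates: ln(0.65)/ln(0.75) = 1.497.
- Schoenfeld power, two-sided: Φ(√(102 × 1/3 × 2/3) × ln 1.497 − 1.96) = 48% (61% one-sided).
- Two-proportion power: 51% two-sided, 63% one-sided.

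The 93% does not reproduce from these inputs. That is a separate and larger problem that group delivery does not cause. Below, the 93% is used once, at face value only.

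**Inputs for the clustering check.** From the article: 120 SRP and 240 TBRI dyads, group size m = 3 to 5, and 42 and 60 expected events. Assumed, because the article gives no value for dyads: within-group correlation ρ, net of site, of 0.05 to 0.10.

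**Formulas.**
- Design effect, TBRI arm only: DE = 1 + (m − 1)ρ.
- H1, log hazard ratio: true SE / unadjusted SE = √[(1/42 + DE/60) / (1/42 + 1/60)].
- Actual two-sided α = 2 × [1 − Φ(1.96 / SE ratio)].

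| m | ρ | DE | SE ratio (H1) | actual α |
|---|---|---|---|---|
| any | 0 | 1.00 | 1.000 | 5.0% |
| 3 | 0.05 | 1.10 | 1.020 | 5.5% |
| 4 | 0.05 | 1.15 | 1.030 | 5.7% |
| 5 | 0.05 | 1.20 | 1.040 | 6.0% |
| 3 | 0.10 | 1.20 | 1.040 | 6.0% |
| 4 | 0.10 | 1.30 | 1.060 | 6.4% |
| 5 | 0.10 | 1.40 | 1.079 | 6.9% |

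**Weighting by dyads.** The table weights the arms by the event counts of the planning scenario. With equal event rates, or for a mean with equal variances, the weights follow the numbers of dyads: variance ratio = (1/120 + DE/240)/(1/120 + 1/240) = (2 + DE)/3. Over m = 3 to 5 the SE ratio is then 1.017–1.033 at ρ = 0.05 and 1.033–1.065 at ρ = 0.10. Actual α is 5.4–5.8% and 5.8–6.6%. These figures serve for the secondary outcomes, and for H1 strictly under the null.

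**Outside the assumed range.** At ρ = 0.01 the H1 ratio is 1.004–1.008. At ρ = 0.20 it is 1.08–1.15, but nothing in the article points to a value that high. At ρ = −0.02 it is 0.98–0.99, so the unadjusted SE would be slightly too large.

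**What it does to precision.** With m = 4, the 240 TBRI dyads carry the information of about 240/1.15 = 209 (ρ = 0.05) or 240/1.30 = 185 (ρ = 0.10). If the stated 93% is accepted, power falls to about 91.5% or 90%.

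**The case against.** The strongest reply is that this is a condensed article and the analysis plan is not shown. Lower-level random terms and variance estimators usually sit there, and nothing in the article excludes a group term. This carries weight for H1, which gets one sentence. It carries less for the secondary outcomes, where the random effects are written out and contain site only.

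Several stronger readings are tempting, and the article does not support them:

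- *Every SRP-versus-TBRI standard error is too small.* This needs a positive within-group correlation, which the article neither gives nor implies. The primary outcome also occurs after discharge, over follow-up to 18 months, when youth live in separate homes; that argues against a high value. H4 is modelled separately, with its own clustering and bootstrap.
- *H1 treats all dyads as independent.* No cluster term is named, but PROC GLIMMIX, a mixed-model procedure, is listed beside PROC PHREG, and the Discussion mentions multilevel modelling. Neither mention shows a training-group term, but independence is not stated.
- *Group-mates keep the same peers and practitioner throughout.* The article does not say that membership is fixed, that youth and caregiver groups hold matching dyads, or which assistant leads which group. Individual make-up sessions loosen the grouping further.
- *SRP is ungrouped.* This is inferred. The content of standard practice is not described, and facility services may themselves be delivered in groups.
- *The error favours TBRI.* The excess error is two-sided and gives no direction.

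What remains is that clustering is designed into one arm and no term is named for it.

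**Conclusion.** The point holds in conditional form. The SRP-versus-TBRI comparison is partially nested, and the H1 and secondary analyses as written name no training-group term. If outcomes correlate positively within training groups beyond what site explains, the standard errors are understated.

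The effect is modest. For assumed correlations of 0.05 to 0.10 and groups of 3 to 5, the true H1 standard error is about 2–8% above the reported one. Actual two-sided α is about 5.5–6.9% (5.4–6.6% when weighted by dyads). At zero correlation nothing is wrong. The result rests on the assumed correlation, on stable groups of the stated size, and on SRP having no comparable grouping. H2 and H4 are outside the point. It is worth settling because the primary contrast is involved and group membership is hard to reconstruct if it is not recorded at delivery.

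**What to change.** 1. Record training-group membership at delivery, with separate youth, caregiver and nurture-group IDs if their composition differs. For youth outcomes, including the primary one, the youth group is the natural cluster. Keep the assigned group for dyads who make up sessions individually.
2. Secondary outcomes: keep site as a random effect in PROC MIXED and add a random training-group effect in the TBRI arm only, with each SRP dyad as its own cluster.
3. H1: in PROC PHREG, use a sandwich variance clustered on training group, or a group frailty. At 3 to 5 dyads per group, 240 TBRI dyads form about 48 to 80 groups (240/5 to 240/3), which together with 120 single SRP dyads gives 168 to 200 clusters. Say whether H1 also carries a site term, since the text leaves that open.
4. If the analysis plan already contains such terms, a cross-reference is enough.

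The cost is one ID variable (up to three if groups differ), one model term or variance option, and slightly wider intervals. If the correlation turns out near zero, little precision is lost.
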